#### Covariates

Demographic variables for age at time of service, gender identity, sexual orientation, race/ethnicity, housing status and insurance status will be developed in accordance with existing SFDPH reporting guidelines. Gender identity will be determined by information on each person’s sex at birth as well as self-reported gender identity to create categories for cisgender male or female, transgender male or female, and genderqueer or nonbinary. Sexual orientation is based on self-report. Race and ethnicity are recorded separately in both EHR systems and will be cross-referenced and then combined into a single variable by replacing race with ethnicity for those who identify as Hispanic/Latinx [22]. SFDPH defines someone as a person experiencing homelessness if they utilize a service that indicates housing instability (e.g., emergency shelter) or self-report homelessness while accessing health care services. Insurance status at the time of an encounter will be based on EHR billing records and grouped into descriptive categories (e.g., private versus public insurance). A location variable using zip code will be based on last location documented prior to the crisis episode. Multiple imputation will be used to account for missing data.

Diagnoses associated with service encounters will be categorized using the primary ICD-10 diagnostic code based on the Health Care Utilization Project’s Clinical Classifications Software Refined (CCSR) [23]. Given the unreliability of diagnosis data at the time of a crisis encounter [24, 25], we will use diagnoses made in routine service settings in the 90 days prior to the index crisis episode and, only if routine care is unavailable, will use acute-care settings diagnoses.

Additional clinical variables will include whether the index crisis episode resulted in an involuntary psychiatric hold; suicidality as part of the presentation (based on ICD-10 Z codes as well as clinical documentation or indication for involuntary holds as “danger to self”); and violence risk (based on clinical documentation or indication for involuntary holds as “danger to others”) [26]. We will also control for continuous variables describing the number of crisis services, routine care, jail, or housing assessment encounters in the 12-months prior to the index crisis episode. We will also assess the number of crisis services, routine care, jail, or housing assessment encounters in the 12-months prior to the index crisis episode.

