### Program

The Behavioral Health Services division of the San Francisco Department of Public Health (SFDPH) has an extensive infrastructure for mental health and substance use disorder services, yet one important gap has remained: real-time response for people in behavioral health crisis in the streets. In 2019, San Francisco’s 9-1-1 call data indicates that approximately 50,000 behavioral health related calls were received, most of which were responded to by a law enforcement unit. Because most calls were not related to criminal events, and instead to mental health and social needs experienced by PEH, San Francisco behavioral health and governmental leaders worked with community stakeholders to create the SCRT to respond as an alternative able to be more responsive to behavioral health crises that happen on the street [16].

The SCRT was designed based on previous co-responder models [17, 18]. To meet the goal of diverting calls that would typically go to the San Francisco Police Department, this trauma-informed specialty behavioral health team is dispatched solely by 9-1-1 operators. The SCRT utilizes a co-responder model comprised of a behavioral health clinician, a paramedic from the San Francisco Fire Department and a peer specialist. Each team member plays a role in providing care including immediate stabilization of urgent medical need (paramedic), de-escalation of the crisis (behavioral health clinician) and person-centered peer support (peer specialist). The team triages clients to the appropriate level of care, be it through resolution of the crisis in the field, linkage to outpatient mental health and substance use services, or transport to an acute treatment setting. The SCRT was first piloted in San Francisco’s highest demand neighborhoods in December 2020 and then was incrementally expanded to be citywide by June 2021 (Fig 1).

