#### Study population

The SCRT aims to provide specialty mental health response and enhanced resources to adults in San Francisco who experience crises related to mental health and/or substance use disorders and are experiencing homelessness. Therefore, the study population will be defined based on age greater than 18 years, meeting criteria for homelessness in the 12 months prior to or 3 months following the crisis episode, and receipt of crisis care from any of San Francisco’s “front door” programs for people in an acute behavioral health crisis. These settings include two mobile crisis programs (Comprehensive Crisis Services and the SCRT), a crisis stabilization unit (DORE Urgent Care Clinic), and emergency psychiatric services (Zuckerberg San Francisco General Hospital’s Psychiatric Emergency Services [PES] and Emergency Department visits with a primary behavioral health diagnosis) (Fig 2). The population of housed adults utilizing acute behavioral health services will be utilized as a control group in the ITS sensitivity analyses.

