This analysis will use several design and analysis strategies to account for potential threats to internal validity. First, the study design using two nonequivalent groups with staggered implementation (crisis episodes with zip codes corresponding to neighborhoods that did or did not have the SCRT active during the partial implementation phase prior to citywide expansion) will allow for a between-site comparison of the pilot catchment area relative to the non-pilot areas (Fig 1). Additional sub-analyses will examine within-site differences for the pilot neighborhoods across the three time periods, and, separately, within-site differences for the non-pilot neighborhoods. Second, a non-equivalent non-treatment control group (non-homeless adults accessing crisis services) will be compared to the target population (homeless adults accessing crisis services) using a difference of differences approach to account for secular variations in mental health and substance use service utilization. Third, a series of non-equivalent dependent outcome variables that are not expected to be impacted by the implementation of the SCRT (e.g., non-crisis initiation of outpatient mental health services) will be evaluated across the same time periods with a similar goal of accounting for secular variations in mental health service utilization. Additional issues such as autocorrelation of repeated measures on individuals will be corrected for in the final analyses.

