### Limitations

There are several limitations to the research methods described above. While ITS designs can measure the impact of a non-randomized intervention, this quasi-experimental approach may not yield definitive results and may be specific to San Francisco and therefore less generalizable to other regions. The electronic records used to describe health, housing and jail service utilization does not capture all services provided in settings outside of the San Francisco Department of Public Health. Though data from 9-1-1 dispatch might help identify which cases are being diverted from SFPD to the SCRT, these data will not be available for this evaluation. It is not possible to fully account for the potential impacts of COVID on data collection and service utilization. Incomplete data on the location of PEH may impede any location-specific analysis; in this case, only the pre-pilot and full implementation segments would be included in the ITS. Limitations in the semi-structured interviews may include sampling bias that results from recruitment through the clinical program, the difficulty of locating potential participants, and the need to exclude potential participants who do not have capacity to consent due to psychiatric or other symptoms; recall bias related to traumatic experiences while in crisis; and desirability bias due to difficulty describing negative experiences of the health care system.

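### The pilot versus non-pilot comparison assigns SCRT exposure from a pre-crisis zip, and nothing in the plan handles a zip that is recorded but wrong

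*Protocol article*

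**What the plan says.** The only location variable defined in the protocol article is in the Covariates section: "A location variable using zip code will be based on last location documented prior to the crisis episode". For missing values, the same section says "Multiple imputation will be used to account for missing data".

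The Interrupted time series analysis section lists the staggered rollout first among its protections of internal validity. It forms the two groups from "crisis episodes with zip codes corresponding to neighborhoods that did or did not have the SCRT active during the partial implementation phase", and says this "will allow for a between-site comparison of the pilot catchment area relative to the non-pilot areas". Sub-analyses within the pilot neighborhoods, and separately within the non-pilot neighborhoods, rely on the same split.

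The Program section describes the gap that SCRT fills as "real-time response for people in behavioral health crisis in the streets", with dispatch through 9-1-1 only and a launch in selected neighborhoods. The Study population section takes in people "meeting criteria for homelessness in the 12 months prior to or 3 months following the crisis episode".

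Under Limitations, the plan concedes: "Incomplete data on the location of PEH may impede any location-specific analysis". Its fallback is that "only the pre-pilot and full implementation segments would be included in the ITS". The same section says that 9-1-1 dispatch data will not be available.

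**The concern.** Whether SCRT could attend a crisis during partial implementation depended on where the crisis took place. The plan infers this from a zip recorded earlier. For someone without stable housing, that zip may be an old address, a shelter or a clinic in another part of the city. Some episodes would then be counted in the wrong area.

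The two protections in the plan, imputation and the fallback, respond to location that is absent. A zip that is present but out of date passes through both.

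At stake is the only concurrent comparison made within the homeless population. The other two strategies use housed adults and different outcomes. If the areas are partly mixed, a null between-area result could mean either that SCRT had no effect or that the split was poor, and the plan offers no way to tell which.

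**Working it through.** **Inputs.** The article gives no sample size, effect size, outcome rate, share of episodes in pilot areas or zip accuracy, so there is no figure of its own to reproduce. Everything below except the calendar dates is assumed.

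**Step 1: the formula.** Let q be the share of crises truly in active areas, and s the probability that the recorded zip puts an episode in the right area (the same in both directions).

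- PPV = qs / [qs + (1 − q)(1 − s)]
- NPV = (1 − q)s / [(1 − q)s + q(1 − s)]

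Episodes labelled pilot carry PPV of the true effect, and those labelled non-pilot carry 1 − NPV of it. The observed difference is therefore the true difference × (PPV + NPV − 1), if errors are non-differential and stable.

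Worked case, q = 0.3 and s = 0.8: PPV = 0.24/0.38 = 0.632, NPV = 0.56/0.62 = 0.903, factor = 0.535.

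| Accuracy s | Factor, q = 0.5 | A 5-point effect shows as | Factor, q = 0.3 or 0.7 | A 5-point effect shows as |
|---|---|---|---|---|
| 90% | 0.80 | 4.0 | 0.75 | 3.7 |
| 80% | 0.60 | 3.0 | 0.54 | 2.7 |
| 70% | 0.40 | 2.0 | 0.35 | 1.7 |

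The within-site analyses are affected too. At q = 0.5 and s = 0.8, the pilot neighborhoods would show 0.8 × 5 = 4 points during partial implementation. The non-pilot neighborhoods would show a spurious 0.2 × 5 = 1 point.

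**Step 2: what this does to power.** Assume 30% versus 35%, two-sided alpha 0.05, 1,377 independent episodes per area and q = 0.5. Power is 80% with correct location, and 61%, 39% and 20% at 90%, 80% and 70% accuracy. Sample size for the same power grows by 1/factor²: about 1.6, 2.8 and 6.3 times.

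**Step 3: errors related to risk.** Take q = 0.5, s = 0.8, a 30% base risk and an SCRT effect of +5 points in every episode. Let non-pilot episodes wrongly labelled pilot have base risk shifted by r points, and pilot episodes wrongly labelled non-pilot by −r.

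- Labelled pilot: 0.8 × 35 + 0.2 × (30 + r)
- Labelled non-pilot: 0.8 × 30 + 0.2 × (35 − r)
- Difference: 3 + 0.4r

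For r = −10, 0 and +10, the observed difference is −1, +3 and +7 points.

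Before SCRT, the same sums without the 5-point effect give 0.4r. Comparing changes from baseline therefore removes the fixed part and returns 3 points, the 0.60 dilution. Bias in either direction thus arises in a comparison of levels, or if r or s changes between periods.

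**Step 4: the calendar.** Partial implementation runs from December 2020 to July 2021, 8 months. The Program section has SCRT citywide by June 2021. In up to 2 of those 8 months (June and July) there may be no inactive area at all. A check of SCRT encounters against inactive zips is therefore informative for December 2020 to May 2021, 6 months, and only for zips not yet active at the time.

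**The case against.** **The rule has a good rationale.** Episodes enter through mobile teams, a crisis stabilization unit, PES and the ED. For facility episodes, a contact zip would be that of the facility, and dispatch data are unavailable. A zip recorded before the crisis can be applied alike to every entry point and period, and SCRT contact cannot alter it. Using the crisis site only where it is known would make measurement depend on entry point, and so on treatment. This stands, and it is why the rule should be kept. A reader might infer that the rule should be replaced by crisis-site zip; the documents identify no source that could supply one for all episodes.

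**A condensed article leaves operational detail elsewhere.** The lack of a stated lookback is not an error in itself. What remains is that the article fixes a definition and puts it to a use that it does not fit. Reading the phrase about crisis-episode zips as the crisis site does not help: the two sections would then describe different variables and would need reconciling.

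**Location is already a stated limitation.** True, but only for incomplete data.

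**Dilution is not certain.** A reader might infer that the SCRT effect will necessarily be understated. That needs non-differential, stable errors, which the document does not establish. How recent a zip is may depend on prior service contact, which may relate to the outcomes. Limitations also says that COVID's effects on data collection and service use cannot be fully accounted for.

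**A hard recency cutoff has its own bias.** It selects people with recent service contact, while routine care and crisis reutilization are outcomes. This stands, so such a cutoff belongs in a sensitivity analysis.

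**Conclusion.** The point holds for the pilot versus non-pilot comparison and the within-site sub-analyses. Exposure there rests on a pre-crisis zip, true exposure follows the place of the crisis, and no stated safeguard covers a recorded but outdated zip.

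The size cannot be calculated from the document. Under non-differential, stable error and assumed accuracy of 90% to 70%, between 0.80 and 0.40 of the true difference survives at a 50% pilot share, and between 0.75 and 0.35 at 30% or 70%. If zip currency relates to outcome risk, the bias can run in either direction.

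A reader might extend this to the evaluation as a whole. The documents do not support that. The three-period citywide analysis assigns exposure by calendar month, and neither the housed control group nor the non-equivalent outcomes depend on zip for exposure. This should be addressed before the between-area result is interpreted, but it does not undermine the main analysis.

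**What to change.** Keep the pre-crisis zip as the common location source for all episodes, and add the following:

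1. A sensitivity analysis restricted to recently documented zips, with the window named in advance, and a statement that it selects people with recent service contact.
2. A table, for SCRT encounters in the months before citywide coverage only, of the share assigned to a zip that was not yet active. This estimates one direction of error (active-area crises placed in inactive zips), among SCRT recipients, on the assumption that teams stayed within their active areas. It says nothing about inactive-area crises given a pilot zip.
3. A quantitative bias analysis reported beside the between-area effect. It would use the share from item 2 for one direction and a stated range for the other, and apply PPV + NPV − 1 with the pilot share made explicit.
4. Wording under Limitations that extends both the caveat and the fallback to misclassified as well as missing location.

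The dates and zips needed are already in the planned limited dataset. The cost is some wording, one table and a little more analysis. The restricted analysis will be less precise because episodes without a recent zip drop out of it.

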#### Interrupted time series analysis

The ITS analysis will examine three periods: 1) Pre-SCRT baseline (November 2019 to November 2020), 2) SCRT partial implementation (December 2020 to July 2021), and 3) SCRT full implementation (August 2021 to August 2022). Each of the outcome measures will be computed as a monthly proportion, with the numerator equaling the number of individuals meeting criteria for each outcome and the denominator equaling the total target population in a given month. Using month-long time intervals would yield between 8 and 12 data points per time period, though the final interval length may change depending on the trade-offs between length of observation and statistical power.

Generalized estimating equations (GEE) will be used, with robust standard errors to account for within-person correlation [27], to analyze the trends in outcomes pre-implementation, during partial implementation, and after the implementation of SCRT. Models will include a variable for time (month) after the beginning of our observation period, a variable for time each time period subsequent to baseline, and the interaction between these variables to assess change in the trajectory of each outcome. Models will be adjusted by the covariates described above and interaction terms constructed to understand the relative effects of covariates and the ITS variables.

This analysis will use several design and analysis strategies to account for potential threats to internal validity. First, the study design using two nonequivalent groups with staggered implementation (crisis episodes with zip codes corresponding to neighborhoods that did or did not have the SCRT active during the partial implementation phase prior to citywide expansion) will allow for a between-site comparison of the pilot catchment area relative to the non-pilot areas (Fig 1). Additional sub-analyses will examine within-site differences for the pilot neighborhoods across the three time periods, and, separately, within-site differences for the non-pilot neighborhoods. Second, a non-equivalent non-treatment control group (non-homeless adults accessing crisis services) will be compared to the target population (homeless adults accessing crisis services) using a difference of differences approach to account for secular variations in mental health and substance use service utilization. Third, a series of non-equivalent dependent outcome variables that are not expected to be impacted by the implementation of the SCRT (e.g., non-crisis initiation of outpatient mental health services) will be evaluated across the same time periods with a similar goal of accounting for secular variations in mental health service utilization. Additional issues such as autocorrelation of repeated measures on individuals will be corrected for in the final analyses.

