#### Index crisis episode

Conducting an ITS that includes a time-dependent outcome—in this case a routine care episode, acute care episode, housing assessment, or jail entry within 30 days following a crisis episode—requires defining an index crisis episode to start the clock for the outcome time interval. Furthermore, given that there may be multiple index episodes per unique individual, the index crisis episode needs to be defined per ITS interval, which, based on our preliminary power analysis, will be divided as one calendar month per interval. The index crisis episode will therefore be defined as the first instance in a given month that an individual has a crisis episode, with the 30-day post-crisis outcome period trailing the end date of the index episode.

We also need to account for the fact that a single crisis episode may result in multiple contacts with different settings in the acute behavioral health care system. To account for this variability, we will use our clinical knowledge of common care pathways as the basis for a crisis system map (Fig 2) that defines different sequences of care as either a step-up in service intensity (e.g., mobile crisis followed by crisis stabilization or ED), a step-down in service intensity (e.g., PES followed by crisis stabilization), or a distinct crisis episode that mostly likely signifies reutilization (e.g., PES followed by mobile crisis, or two consecutive mobile crisis episodes). We will then combine sequences with a step up or down in service intensity that occur within two or fewer days between the end of the first and start of the second clinical setting, so as not to miscount these care transitions as reutilization. This approach also allows us to create a variable describing these crisis system trajectories, thus allowing us to identify potential differences between index crisis episodes based on crisis system entry point and end point. All crisis services utilized three or more days after the index crisis episode end date will be considered separate from the index crisis episode.

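### The 30-day outcome windows of November 2020 index episodes run into December 2020, when SCRT launched in pilot areas, so the last pre-SCRT baseline point is partly exposed and no rule handles it

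*Protocol article*

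**What the plan says.** Four statements in the protocol article fix the point.

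- **Interval** (Index crisis episode): the time series "will be divided as one calendar month per interval".
- **Index and window** (same section): the index episode is "the first instance in a given month that an individual has a crisis episode, with the 30-day post-crisis outcome period trailing the end date" of that episode.
- **Periods** (Interrupted time series analysis): the first two segments are "Pre-SCRT baseline (November 2019 to November 2020), 2) SCRT partial implementation (December 2020 to July 2021", and the third, full implementation, runs from August 2021 to August 2022. Each outcome is a monthly proportion over that month's target population.
- **Launch** (Program): the team was "first piloted in San Francisco’s highest demand neighborhoods in December 2020 and then was incrementally expanded to be citywide by June 2021". The text gives no day in December, and Fig 1, which carries launch dates, is not shown here.

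Two definitions bear on the mechanism. Study population lists SCRT among the crisis settings, and Outcome variables counts any crisis care episode in the 30 days after discharge as reutilization. The article describes no washout, transition month or censoring rule for windows that cross a period boundary.

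**The concern.** A month is labelled by when the crisis happened, but its outcome is collected afterwards. An episode ending on day d of November 2020 has d of its 30 follow-up days in December. Where SCRT was then active, it could act inside that window:

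- **Reutilization.** A December SCRT contact is itself a crisis episode, so it can be the outcome event of an index episode coded as pre-SCRT.
- **Jail entry.** The Program section says SCRT was created to take calls that would usually go to the police. A new crisis in December may therefore be met differently from one in November.
- **Routine care and housing assessment.** Linkage, and follow-up by the Office of Coordinated Care, come after an SCRT encounter. For a November index case they would need a new SCRT contact inside the window.

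November 2020 is the end point of the baseline, where a straight line has its highest leverage. An early SCRT effect in that point tilts the projected counterfactual toward post-launch values, and the estimated level change tends to shrink.

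**Working it through.** **The plan's own figure.** The article states no overlap share. Its only related number is 8 to 12 monthly points per period. Counting the stated dates gives 13, 8 and 13 months, so the upper end does not reproduce. That is a separate matter; the baseline is taken as 13 points below.

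**Step 1: share of follow-up days after launch.** Inputs from the article are the 30-day window from episode end, the calendar-month interval and launch in December 2020. Launch day, timing of episodes within the month and episode length are not given, so they are assumptions and are varied.

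- Same-day episodes, even timing, launch 1 December: mean of d/30 for d = 1 to 30 = 15.5/30 = 0.517.
- Taking the first episode in the month shifts index dates earlier. With weights 31 − d: 4960/13950 = 0.356. With weights exp(−λ(d−1)/30), the share is 0.475, 0.435, 0.360 and 0.298 for λ = 0.5, 1, 2 and 3 episodes per person-month.
- Launch 8 December, even timing: (1 + … + 23)/900 = 276/900 = 0.307.
- Launch 15 December, even timing: (1 + … + 16)/900 = 136/900 = 0.151.
- Episodes of 3 or 7 days, launch 1 December, even timing: 549/900 = 0.610 and 647/900 = 0.719.

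Over all combinations tried the range is about 5% to 72%. With short episodes and launch on 1 December, every November window crosses the boundary, by 36% to 52% on average for timing from moderately early to even.

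**Step 2: leverage of the last baseline point.** For an equal-weight line through months t = 1 to 13, the mean is 7 and Sxx = 182. The weight of month 13 on the projection to month t* is 1/13 + (t* − 7) × 6/182. At December 2020 (t* = 14) this is 0.077 + 0.231 = 0.308.

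**Step 3: effect on the level change at launch.** Let c be the fraction of the initial effect carried by the November 2020 point. The understatement is c × 0.308.

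- *Effect in proportion to exposed days, half exposed (c = 0.5):* 0.5 × 0.308 = 0.154. A 34-month segmented least-squares fit with a true step of 1 and c = 0.517 agrees: the level change is 0.841, with a false baseline slope of 0.017 per month.
- *Effect only through a repeat crisis answered by SCRT:* assume a fraction r has a repeat crisis within 30 days, half of these fall after launch, and SCRT answers the same share of repeat as of index crises. After launch there are 1 + r opportunities for contact per person; for November index cases there are 0.5r. So c = 0.5r/(1 + r). For r = 0.1, c = 0.05/1.1 = 0.045 and the understatement is 0.014. For r = 0.5, c = 0.25/1.5 = 0.167 and the understatement is 0.051.

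**The case against.** **Index-date coding is legitimate.** If the exposure is the response at the index crisis, a person indexed in November was not exposed. This stands for effects that begin at the index contact, and it is why the lower range in the working may be nearer the truth for linkage and housing. It does not dispose of reutilization or jail entry, where SCRT can act on events inside the window whoever answered the index crisis.

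**The launch was a pilot.** December days outside the pilot neighborhoods were unexposed. That lowers the absolute spill-over, but partial coverage dilutes the December effect as well, so the understatement as a share of that effect is not reduced for this reason. The planned within-site analysis of pilot neighborhoods has no such dilution; the one for non-pilot neighborhoods should have no local spill-over.

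**It is one month of 13, and the weights are illustrative.** True. The planned model is a covariate-adjusted GEE, not equal-weight least squares, so the percentages show order of magnitude only. The month is, however, the end point.

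**This belongs in an analysis plan.** A sensitivity analysis might. Here the article itself fixes the window, the interval and the cut-point, and the misclassification follows from those three together. The housed control group and the non-equivalent outcomes address secular change, not exposure at the boundary.

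**Conclusion.** The point holds in a limited form: the last baseline month is partly exposed, the plan does not handle it, and the likely direction is understatement of the change at launch. The size is roughly 1% to 5% of the initial effect if a repeat SCRT contact is needed, and about 15% if the effect follows exposed days with half the window exposed. The second figure scales with the exposed share, so it falls with a later launch day and rises with longer episodes. All of this rests on assumed launch day, episode timing, episode length and repeat fraction.

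Three stronger readings are not supported.

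- A reader might infer that November 2020 is measured mostly after launch. The share is about half in the simplest case, lower under the first-in-month rule or a later launch, and clearly above half only if episodes last several days.
- A reader might carry the end-point weight forward to August 2022 (1/13 + 27 × 6/182 = 0.967) and report a shift of nearly half the effect. That would be a share of the first-month pilot effect, not of the full-implementation effect, and it needs the exposed-days assumption.
- A reader might assume that linkage and follow-up reach all November cases. They require an SCRT encounter.

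The same overlap at July/August 2021 matters less, because coverage was citywide by June 2021.

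**What to change.** In Interrupted time series analysis, state that November 2020 is a transition month outside the baseline segment, so that baseline runs from November 2019 to October 2020 (12 months). Index episodes ending by 31 October have windows that close by 30 November, before launch. Report the model with November 2020 kept in baseline as a sensitivity analysis, for all four outcomes.

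Dropping only the November episodes whose windows cross launch is not a workable substitute: with launch on 1 December, a rule excluding episodes that end less than 30 days before launch leaves only those ending on 1 November.

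The cost is a sentence or two of analysis wording and one of 13 baseline months, hence a slightly wider interval. Data collection does not change.
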